C. (Group 3): the Clinical Global Impressions Scale is a 3-item, researcher-administered tool that provides an overall ‘global’ judgement concerning the participant’s severity of depressive illness.

D. (Group 1): TICS-M is a short, researcher-administered assessment of cognitive functioning validated for use over the phone.

E. (Group 3): the Inventory of Depressive Symptomatology (30-item Clinician Rated)^75^ is a researcher-rated instrument that provides detailed assessment of depression severity over the previous 7 days.

### Verbal cognitive and speech tasks

All participants will complete the same sequence of verbal cognitive and speech assessments. An overview of speech tasks is provided in table 2. Some of the tasks are optimised to elicit continuous narrative speech, such as reading text and recalling a presented story. Others elicit specific categories of words, or repetition of sentences or sounds.

These tasks combined allow for evaluation of a range of cognitive, linguistic and acoustic features elicited during spoken responses. Differential impairments are expected across groups and tasks, for example, while neurodegenerative cognitive disorders such as AD are commonly associated with anomia and decreased information content, other neurodegenerative conditions such as PD show greater impairment in volume and articulation.^53 56^ Language-based changes have also been noted in PD including rates of pauses, phrase length and changes in sentence generation and construction.^76^ Similarly, cognitive and speech changes in mood disorders are commonly described.^52 77–79^

The consistent use of tasks across groups allows for a head-to-head comparison of task performance and speech measures for different clinical indications and different tasks. The tasks are selected due to a rich research background showing their involvement in specific clinical indications (described in table 2). However, with a few notable exceptions, cross-diagnostic evaluations are not commonly reported.

Speech tasks will be administered and recorded using the application, with all participants completing the same set of speech tasks. Participants will be supported with using the Novoic application on their smartphone. Audio recordings will be transferred to a secure server and then deleted from the smartphone device.

Recordings of the combined screening and baseline visit will also be made simultaneously by video conferencing software. Zoom (https://zoom.us) will be used due to its ability to turn off audio manipulation effects. The main assessment phase begins with a series of speech tasks, self-recorded using a smartphone application, that the researcher guides the participant to complete. An overview of the specific tasks completed in the main assessment is provided in table 3.

**Table 3 T3:** Assessments completed during main (supervised) assessment, and remotely via the application on the participants’ own smartphones

Task	Main (supervised) assessment	Remote assessment day											

Participants will then complete follow-up data collection over a period of 4 weeks using the smartphone application. Participants will be notified via the mobile application to complete 12 brief (approximately 15 min) unsupervised speech and cognition assessments over the month following the baseline visit. Participants will receive a different set of speech tasks each day from the application’s built-in task-bank, including the same main speech and cognition tasks described above, and abbreviated test of executive function (Stroop, digit span).

Additional, brief self-report measures, incorporated into remote assessments, included:

A 4-item questionnaire on the usability of the smartphone application.A brief, 3 min long questionnaire on whether the participant has any visual or hearing impairments, and whether they had related difficulties with the administered tasks.A baseline 4-item questionnaire: examining typical mood, sleep, mind wandering and effort.A brief, daily 4-item questionnaire on current state: mood, sleep, mind wandering and effort.

The remote assessment schedule is provided in table 3. Participants will also complete follow-up questionnaires online via Qualtrics during weeks 2 and 4, which are shown in table 1.

### Statistical analysis plan

The main analysis objectives of the study include examining: (1) feasibility of eliciting and collecting speech data within different clinical groups, (2) reliability, and intrasubject and intersubject variance of speech task performance, (3) adherence to remote unsupervised assessments, (4) app usability and (5) to evaluate whether acoustic and linguistic patterns can be used to distinguish between clinical indications and controls.

Feasibility will be assessed as the length of speech generated during speech elicitation tasks. The primary end point is calculated as the number of participants who successfully complete Automated Story Recall Task (ASRT) assessments as a fraction of the disease cohort, which may indicate likely suitability of this procedure within each disease group. Participants are considered successful where at least one of the immediate story recalls produces a spoken response spanning ≥20 s from the first to the last word. The effect of demographic confounders (age, sex and education) on task feasibility will be evaluated.

Reliability will be measured by examining the stability of equivalent tasks completed over the assessment period. This will include examining reliability across parallel test variants that vary by assessment day and by setting (baseline vs remote follow-up).

Practice and learning effects of parallel test variants over repeated assessment will be characterised with linear mixed effects models. Correlational analysis will be completed between parallel test variants, and intraclass correlations will be carried out to examine test–retest reliability of the same test variants administered across days and between settings (virtual study visit vs remote assessment). Coefficients of individual agreement will be used as a measure of interparticipant and intraparticipant variability.

Usability will be examined via the scores on the usability questionnaire for each disease cohort and their matched controls to examine disease cohort-specific problems or difficulties in completing remote assessments. Adherence will be defined as the proportion of participants engaging in daily remote assessments in each indication. Data will be analysed using t-tests, analysis of variance or non-parametric equivalents, as appropriate. Age and education differences between groups will be controlled for as appropriate.

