**Methods and analysis:**

The present study will assess the feasibility of obtaining speech data, collected remotely using a smartphone app, from individuals across three NPD cohorts: neurodegenerative cognitive diseases (n=50), other neurodegenerative diseases (n=50) and affective disorders (n=50), in addition to matched controls (n=75). Participants will complete audio-recorded speech tasks and both general and cohort-specific symptom scales. The battery of speech tasks will serve several purposes, such as measuring various elements of executive control (eg, attention and short-term memory), as well as measures of voice quality. Participants will then remotely self-administer speech tasks and follow-up symptom scales over a 4-week period. The primary objective is to assess the feasibility of remote collection of continuous narrative speech across a wide range of NPDs using self-administered speech tasks. Additionally, the study evaluates if acoustic and linguistic patterns can predict diagnostic group, as measured by the sensitivity, specificity, Cohen’s kappa and area under the receiver operating characteristic curve of the binary classifiers distinguishing each diagnostic group from each other. Acoustic features analysed include mel-frequency cepstrum coefficients, formant frequencies, intensity and loudness, whereas text-based features such as number of words, noun and pronoun rate and idea density will also be used.

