### Study objectives

The primary objective of the study is to evaluate the feasibility of eliciting continuous narrative speech to collect speech data remotely in three groups of NPDs: neurodegenerative cognitive disorders, other neurodegenerative disorders (PD and MND) and affective disorders. We hypothesise that due to the simple speech-based interface, participants will be able to engage with and provide speech data during virtual study visits and remote assessments. Basic feasibility will be assessed via the average length of speech elicitation for each speech task (in seconds) during the first week of self-assessment. Additionally, we will examine the proportion of participants in whom narrative speech lasting at least 20 s is elicited within each group.

The study also has secondary objectives concerning the feasibility of using speech tasks to collect speech data in the remote setting, such as evaluating reliability of repeated assessments across related (comparing virtual visits vs fully remote assessments) or repeated tasks (parallel variants administered across days), examining intra-individual and inter-individual variance. We will also evaluate adherence to daily remote assessments, and participant-rated usability of the remotely administered application, measured via a brief usability questionnaire completed on the app.

Furthermore, the study will examine whether acoustic and linguistic patterns can be used to distinguish from group-specific control participants, and from other clinical indications, and whether this is impacted by relevant contextual or disease information covariates.

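### The coefficient of individual agreement is named as the measure of inter- and intra-participant variability, but it is an agreement ratio that quantifies neither

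*Protocol article*

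**What the plan says.** The Study objectives section lists, among the secondary feasibility aims, "examining intra-individual and inter-individual variance". The Statistical analysis plan section repeats the aim as item (2) of its main analysis objectives: "reliability, and intrasubject and intersubject variance of speech task performance".

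One statistic is tied to that aim by name: "Coefficients of individual agreement will be used as a measure of interparticipant and intraparticipant variability".

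Two other analyses in the same paragraph involve the relevant variances, and each has a different stated job:

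- "Practice and learning effects of parallel test variants over repeated assessment will be characterised with linear mixed effects models"
- "intraclass correlations will be carried out to examine test–retest reliability of the same test variants administered across days and between settings"

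Nothing in the section says that variance components from either will be reported for the variability aim.

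**The concern.** The coefficient of individual agreement was built to ask whether two methods, settings or occasions can be interchanged for the same person. It compares the disagreement seen when a condition is changed with the disagreement seen when it is merely repeated. Both are differences within one participant, so the spread between participants is not what it measures. It is also unit-free, so it does not give the size of the within-participant variance.

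The article counts the study's ability to describe variability within and between people in each clinical group among its strengths. If the coefficient is reported under that label, a value near 1 could be taken to mean stable participants, or a cohort whose members are well separated. It shows neither. It shows only that changing the condition adds little to ordinary repeat error, and that can happen because the repeat error is large.

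**Working it through.** **Inputs.** The documents state no figure for this point, so there is none to reproduce. The formula is the standard definition of the method and is not printed in the article. Every variance below is an assumption. Only the number of participants per clinical cohort (50), used in a simulation, comes from the article.

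**Definition, for two conditions with replicates.** Let w² be the within-participant variance, i² the participant-by-condition interaction variance, d the mean shift, b1 and b2 the between-participant SDs in the two conditions, and ρ the correlation of true scores.

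CIA = 2w² / [d² + (b1 − b2)² + 2(1 − ρ)·b1·b2 + 2i² + 2w²]

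When b1 = b2 and ρ = 1 (the additive model), both terms in b vanish:

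CIA = 2w² / (d² + 2i² + 2w²)

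The comparator is the intraclass correlation in its consistency form, which leaves out the shift: ICC = b² / (b² + i² + w²).

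**Step 1: does the coefficient respond to between-participant variance?** Take w² = 1, i² = 0.25, d = 0.3.

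CIA = 2 / (0.09 + 0.5 + 2) = 2/2.59 = 0.772, whatever b² is.

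| b² | CIA | ICC |
|---|---|---|
| 1 | 0.772 | 1/2.25 = 0.444 |
| 4 | 0.772 | 4/5.25 = 0.762 |
| 9 | 0.772 | 9/10.25 = 0.878 |

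A second set of assumptions (w = 1, d = 0.5, i = 0.3) behaves the same way. CIA = 2 / (0.25 + 0.18 + 2) = 0.823 at every between-participant SD from 0 to 4, while the ICC runs from 0.00 to 0.94. A simulation with 50 participants, three replicates per setting and 2,000 runs gave 0.827 to 0.830 across that range.

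**Step 2: what if the additive model fails?** Take w = 1, d = 0.5, no interaction.

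| Between-participant SD (first condition) | SD ratio 1.5, ρ = 1 | Equal SDs, ρ = 0.8 |
|---|---|---|
| 0.5 | 0.86 | 0.85 |
| 1 | 0.80 | 0.75 |
| 2 | 0.62 | 0.52 |
| 4 | 0.32 | 0.23 |

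The coefficient now moves, but only through (b1 − b2)² or 2(1 − ρ)·b1·b2, which describe how far the conditions differ. At SD 2 it is 2/(0.25 + 1 + 2) = 0.62 in the first column, 2/(0.25 + 1.6 + 2) = 0.52 in the second, and 2/(0.25 + 2) = 0.89 under the additive model. The SD in the first condition is 2 in all three.

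**Step 3: does it report within-participant variance?** With d = 0 and i = 0 it is 2w²/2w² = 1.00 at within-participant SD 0.5, 1, 2 and 4 alike. With d = 0.5, i = 0.3 and b = 1:

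| Within-participant SD | CIA | ICC |
|---|---|---|
| 0.5 | 0.5/0.93 = 0.54 | 1/1.34 = 0.75 |
| 1 | 2/2.43 = 0.82 | 1/2.09 = 0.48 |
| 2 | 8/8.43 = 0.95 | 1/5.09 = 0.20 |
| 4 | 32/32.43 = 0.99 | 1/17.09 = 0.06 |

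As participants become noisier the coefficient improves and the intraclass correlation collapses.

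**The case against.** Three stronger readings are tempting, and the documents do not support them.

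- **That the variability objective would go unanswered.** The intraclass correlation contains between-participant variance, and a mixed model with a participant random effect estimates both components. Both analyses are planned in the same paragraph. The objective can be met; what is wrong is the statistic assigned to it.
- **That between-participant variance always cancels.** Exact cancellation needs equal between-participant SDs across conditions and true scores aligned apart from an additive interaction. Step 2 shows the coefficient moving when either fails. This qualifies the algebra but does not rescue the coefficient, because what enters is discrepancy between conditions.
- **That the design cannot support the coefficient because there is only one supervised visit.** The plan does not say that the coefficient will compare supervised with remote assessments. One visit also does not rule out replicates within it: Table 2 gives two different sentences at each sentence-task assessment, and Table 3 places sentence repetition in the supervised visit. Table 3 also shows repeated stimuli for story recall, category fluency and letter fluency on days 14, 21 and 28. The limit holds for particular tasks. Action fluency, sustained phonation and script reading have one supervised and one remote session each; Stroop and sequence narration occur once.

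It is also fair to say that this is a condensed article, and that model specification may sit in a fuller plan. The primary endpoint (a story recall of at least 20 s) and the classifier results do not depend on this statistic. That bounds the importance of the point. It does not remove it, since the sentence states a choice of measure that does not fit its purpose.

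**Conclusion.** The point stands as a mis-assigned measure for a stated secondary aim. The coefficient of individual agreement cannot quantify variability between participants: under the additive model it is constant (0.77 in the main illustration) while the intraclass correlation doubles from 0.44 to 0.88. Nor does it report variability within participants, and with a shift or interaction present it rises with noise (0.54 to 0.99 in Step 3).

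The sizes rest on assumed variances. The cancellation does not depend on those values, only on the additive model. Outside that model the coefficient reflects a discrepancy between conditions. The conclusion does not extend to the primary endpoint or the classification analyses, and the data and models needed for the objective are already in the plan.

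**What to change.** Replace the sentence so that the measure of inter- and intra-participant variability is the set of variance components from the planned mixed models: between-participant and residual within-participant, plus participant-by-setting where the task's replicates allow it to be separated from the residual. Report each with a 95% confidence interval, by cohort, alongside the planned intraclass correlation. For tasks recorded only once, state that no such split is available across sessions.

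If the coefficient of individual agreement is kept, describe it as a measure of agreement between settings or days, say which are being compared, and restrict it to tasks with replicate readings.

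The cost is a change of wording and some extra output from models already planned. Data collection and sample size are unaffected.

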Deep learning methods will be used, where the speech measures are derived as internal representations of the models. Methods used here will include unsupervised context-aware word embeddings, a way of distinguishing between identical words with different contextual meanings,^87^ and audio representation learning.^84^

Training and validation of the ML models will be performed using cross-validation techniques. Performance of classification analysis will be characterised by the area under the receiver operating characteristic curve (AUC), sensitivity, specificity and Cohen’s kappa. Demonstration that a binary classifier performs better than the random baseline will be done via mapping AUC estimates to a p value via the Mann-Whitney U statistic.^88^ Results will be contrasted with demographic comparisons (comprising sex, education and age) as in prior analyses,^48^ to evaluate the contribution of demographic imbalances.

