### Participants

Potential participants will be identified through local clinical services, cohort-specific internal databases, advertisements on a variety of social media platforms and dedicated websites for research participation. Participant recruitment began on 15 July 2021 and will continue to 30 June 2022.

Participants will meet group-specific eligibility criteria for neurodegenerative cognitive disorders (n=50), or other neurodegenerative motor disorders (n=50), or affective disorders (n=50), in addition to matched controls (n=75). The sample size was based on a review of feasibility study group sizes.^63^ Individuals must be native English speakers, have access to a smartphone and personal computer/laptop which can connect to the internet and is capable of audio recording as well as running an operating system of macOS X with macOS 10.9 or later; or Windows 7 or above. Exclusion criteria include: current substance use disorder, stroke within the last 2 years, transient ischaemic attack or unexplained loss of consciousness within the last 12 months or current risk of suicide. The additional group-specific eligibility criteria are as follows:

Group 1: neurodegenerative cognitive disorders (n=50): participants must be aged 50–85 years, with a score of 20–30 on The Telephone Interview for Cognitive Status-modified (TICS-M)^64^ and one of the following clinical diagnoses (within the last 5 years):

MCI due to AD or mild Alzheimer’s dementia as per the National Institute of Aging—Alzheimer’s Association core clinical criteria (2011).^65^Probable or possible DLB as per The Dementia with Lewy Bodies Consortium definition.^66^Cognitive impairment (not due to AD/DLB), either diagnosed with behavioural variant frontotemporal dementia,^67^ semantic variant primary progressive aphasia or non-fluent variant primary progressive aphasia,^68^ vascular dementia^69^ or unspecified MCI.

Group 2: other neurodegenerative disorders (n=50):

Participants with MND must be aged 18–85 years and score stage 3 or less on the King’s amyotrophic lateral sclerosis staging system.^70^Participants with PD must be within 5 years of a diagnosis of idiopathic PD according to the UK Brain Bank Criteria, aged between 30 and 85 years, and have a Hoehn and Yahr stage^71^ of ≤2.

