Group 3: affective disorders (n=50): participants with affective disorders must be aged 18–85 years, diagnosed with either major depression or bipolar disorder, in a current depressive episode according to the Diagnostic and Statistical Manual of Mental Disorders, fourth edition (DSM-IV) criteria as assessed by the Mini-International Neuropsychiatric Interview (M.I.N.I.) V.5.0,^72^ of at least moderate severity as assessed on the Clinical Global Impressions Scale.^73^

Group 4: unaffected controls (n=75): approximately 25 unaffected control participants will be recruited for each cohort, matched for gender, age and education levels. Participants will be in otherwise good health; they may experience mild disorders (of metabolic, respiratory, immunological, cardiologic and metabolic origin) that do not impair daily functioning.

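### Between-disease classifiers are formally tested only against chance, and no test of gain is stated for the planned demographic contrast, so a speech score that mainly tracks age could be significant

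*Protocol article*

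**What the plan says.** The Abstract plans "binary classifiers distinguishing each diagnostic group from each other". Study objectives asks whether speech patterns can "distinguish from group-specific control participants, and from other clinical indications". Both disease-versus-disease and disease-versus-control classifiers are therefore intended.

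For inference, the Statistical analysis plan section names one step: "Demonstration that a binary classifier performs better than the random baseline", to be done by converting the AUC to a p value. The p value comes from the Mann-Whitney U statistic, so the null is AUC 0.5. The next sentence reads: "Results will be contrasted with demographic comparisons (comprising sex, education and age) as in prior analyses". Its stated purpose is to gauge how far demographic imbalance contributes. It gives no test, no measure of increment and no criterion.

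Under Participants, the rule for group 1 is "participants must be aged 50–85 years" and for group 3 "participants with affective disorders must be aged 18–85 years". In group 2, the eligible range is 18–85 for motor neuron disease and 30–85 for Parkinson's disease. About 25 controls per cohort are matched on gender, age and education. No matching of the disease cohorts to one another is stated.

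**The concern.** Rejecting AUC 0.5 shows that a score separates two groups. It shows that disease separates them only if the groups are alike in everything else the score can pick up. The article itself treats age, sex and education as potential confounders in its feasibility analysis, and it foresees demographic imbalance in the classifier analysis. Between disease cohorts, the lower age limits differ and no matching is stated, so a small p value against chance is compatible with a score that mostly reads age.

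Setting a speech result beside a demographic result does not settle this. Suppose speech alone gave AUC 0.75 and demographics alone 0.74. Speech might be carrying the same age information, or it might carry largely separate disease information. The two figures look the same in either case. Only a model with both, compared with demographics alone, tells them apart.

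At stake is the fifth main analysis objective, telling clinical indications from one another and from controls. The primary feasibility end point is not affected.

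**Working it through.** The article gives no alpha, target AUC or power for the classifiers, so there is no stated figure to reproduce. The control total agrees: 3 × 25 = 75.

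**Inputs from the article (Participants):** 50 participants per disease group, about 25 controls per cohort, and the age ranges above. **Assumptions made here:** two-sided 5% level; ages uniform over each eligible range unless stated; Parkinson's disease taken as n = 50, since the split of group 2 is not given.

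**Step 1. AUC needed for significance.** The null standard error is √[(n1 + n2 + 1)/(12·n1·n2)].
- 50 vs 50: √(101/30,000) = 0.058; threshold 0.5 + 1.96 × 0.058 = 0.614.
- 50 vs 25: √(76/15,000) = 0.0712; threshold 0.640.

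**Step 2. AUC of age alone.** When group A's age range lies within the range L to U of group B and B is uniform, the AUC is (mean age of A − L)/(U − L).
- Group 1 vs group 3: (67.5 − 18)/67 = 0.739; z = 0.239/0.058 ≈ 4.1.
- Group 1 vs Parkinson's range: (67.5 − 30)/55 = 0.682; z ≈ 3.1.
- Parkinson's range vs group 3: (57.5 − 18)/67 = 0.590; z ≈ 1.5, below the threshold.
- Group 1 vs its own age-matched controls: 0.50.

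**Step 3. How often an age-only score is significant** (2,000 simulated studies per row; p < 0.05 and AUC above 0.5). The score is age plus random noise, with correlation r to age, and has no disease content.

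| Comparison | Ages | r | AUC | Significant |
|---|---|---|---|---|
| Group 1 vs group 3 | uniform | 1.0 | 0.74 | 99% |
| Group 1 vs group 3 | uniform | 0.7 | 0.68 | 90% |
| Group 1 vs group 3 | uniform | 0.5 | 0.63 | 63% |
| Group 1 vs group 3 | uniform | 0.3 | 0.58 | 27% |
| Group 1 vs group 3 | means 72 and 40 (SD 7, 14) | 1.0 | 0.98 | 100% |
| Group 1 vs group 3 | means 72 and 65 (SD 7, 9) | 1.0 | 0.73 | 99% |
| Group 1 vs group 3 | means 72 and 70 (SD 7, 8) | 1.0 | 0.58 | 27% |
| Group 1 vs Parkinson's range | uniform | 1.0 | 0.68 | 90% |
| Group 1 vs Parkinson's range | uniform | 0.5 | 0.60 | 41% |
| Parkinson's range vs group 3 | uniform | 1.0 | 0.59 | 33% |
| Group 1 vs own controls (50 vs 25) | uniform | 1.0 | 0.50 | 2.4% |

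Rows with given means use normal ages cut off at the eligibility limits. The last row is close to the 2.5% expected in the upper tail, so the problem disappears where matching works.

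**The case against.** The best defence is that the article already sees the problem: the sentence after the chance test plans a contrast with sex, education and age for this purpose, so an age-only classifier should show little advantage there. Study objectives also plans to examine the effect of contextual and disease covariates. The contrast follows earlier analyses in a cited study, and the full analysis plan is not shown; either may define it more formally. AUC 0.5 is also the correct null for the literal statement that a classifier beats chance, and no success rule is attached to the p value.

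Much of this stands. A reader might infer that chance is the wrong null for every classifier and that any model detecting age would pass. The documents do not support that. Controls are matched within cohort. Motor neuron disease and group 3 have the same age range. All groups share the upper limit of 85. How large the effect is depends on ages not yet known and on how strongly speech follows age.

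What remains is narrower. The article fixes which comparison carries the p value, and that is the one against chance. The contrast, as worded, compares results and states no test of increment. The separate statement that age and education differences will be controlled for follows the usability and adherence analyses and does not clearly extend to the classifiers.

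**Conclusion.** The point holds for between-disease classifiers, mainly group 1 against group 3 and group 1 against Parkinson's disease. There, significance against 0.5 cannot by itself support the conclusion that speech distinguishes the diagnoses, and the article states no formal test that would.

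The size is conditional. For group 1 against group 3, an age-only score was significant in 27% to 100% of simulated studies across the scenarios shown. These rest on assumed age distributions and assumed correlations between score and age, because the article gives neither. They treat the score as given and do not simulate classifier training. It would go too far to say that an age-only model will pass, or that the plan overlooks demographic confounding. Comparisons with cohort-matched controls are much less affected. Since classification is not the primary end point, this is an advisable improvement to the analysis and does not undermine the study.

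**What to change.** For each patient-versus-patient classifier, make the demographic contrast already planned the formal benchmark:

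- Fit a demographics-only model (age, sex, education) and a demographics-plus-speech model in the same cross-validation folds.
- Report the difference in cross-validated AUC, with a confidence interval from resampling participants, as the main result.
- Keep AUC against 0.5, with its Mann-Whitney p value, as descriptive.

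If the full analysis plan already specifies this, one sentence in the article's Statistical analysis plan section would be enough. The same analysis is optional for patients against their cohort-matched controls.

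No new data are needed. The cost is slightly more computing and a smaller reported effect: against an age-only AUC of 0.74 the largest possible gain is 1 − 0.74 = 0.26, compared with 0.50 above chance. If recruited ages barely overlap (the scenario with age-only AUC 0.98), only 0.02 remains to be gained, and the report should say that the pair cannot show an added contribution from speech outside an age-matched subset.
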